## **METHODS AND ANALYSIS**

### **Study design:**

The study is designed as a multicenter parallel-group non-inferiority randomized controlled trial (RCT) that complies with the CONSORT guidelines (Figure 1). A patient preference arm will be available. Patient recruitment will be done at all university hospital areas of Finland (Helsinki, Kuopio, Oulu, Tampere, Turku). The study is coordinated by Helsinki University Central Hospital, Children's Hospital pediatric orthopedic unit. Trial data analysts and person performing the recruitment will be unaware of the assigned treatment.

### **Patient recruitment:**

All patients with a medial epicondyle fracture referred to the aforementioned hospitals will be screened for eligibility by a specialist of either hand surgery, pediatric surgery, pediatric orthopedics or orthopedics. If inclusion criteria are met, written consent is asked from the guardian. Patients and parents are given a written informed consent regarding the trial. The patient version is age adjusted for easier understanding according to the Finnish Investigators Network for Pediatric Medicines ([www.finpedmed.fi](http://www.finpedmed.fi))

### **Inclusion criteria:**

Patients aged 7-16 years presenting with a  $\geq 2$ mm displaced non-incarcerated medial epicondyle fracture with or without concomitant elbow dislocation and normal ulnar nerve function.

### **Exclusion criteria:**

Pathological fracture, open fracture, systemic bone disease, concomitant fracture or injury of the same upper limb requiring operative intervention, other disease preventing participation in full follow-up regime and range of motion exercises.

## **Randomization**

After agreeing to participation in the trial patients are randomized according to a computer-generated randomization list to either operative or non-operative treatment. Randomization ratio is 1:1.

Randomization is performed by the recruiting physician who is blinded to the intervention.

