#### **Sample size**

Based on the results of Nikolas et al (2020) and Aasheim et al (2014) we assume clinically significant difference between the groups to be 6,8 and the standard deviation of the QuickDASH score to be 10

points. With 0,05 significance level and 80% power a non-inferiority comparison would require 27 patients per group. Allowing a 20% dropout rate the required sample would be 30 patients per group.

For subgroup analysis (less than 12 years vs. 12 years and over) 30 patients per age group needs to be collected. Assuming 50-50 split in the patients between the age groups the sample size would be 60 per ORIF and non-operated equaling a total of 120 patients.

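### The sample is doubled to fill four age-by-treatment cells of 30, but the described randomisation names nothing that balances treatment within age group

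*Protocol*

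**What the plan says.** The Sample size section of the protocol builds its total in two steps. First, on the basis that "we assume clinically significant difference between the groups to be 6,8 and the standard deviation of the QuickDASH score to be 10" points, it states: "With 0,05 significance level and 80% power a non-inferiority comparison would require 27 patients per group". After an allowance for dropout this becomes 30 per group, or 60 children in all. Second, it doubles that figure for one reason: "For subgroup analysis (less than 12 years vs. 12 years and over) 30 patients per age group needs to be collected". It continues: "Assuming 50-50 split in the patients between the age groups the sample size would be 60 per ORIF and non-operated", which makes 120. The total of 60 per arm follows only if 30 is meant for each age group within each arm, so the plan needs four cells of 30.

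The Statistical analysis section confirms that the primary outcome will be examined by the same age cut within each treatment group. It names the Wilcoxon rank-sum test.

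On allocation, the Randomization section says that "patients are randomized according to a computer-generated randomization list", with a literature reference for the list and a 1:1 ratio. No section mentions stratification by age or hospital, blocking, separate lists or an age quota. On sites, the Study design section says: "Patient recruitment will be done at all university hospital areas of Finland", and it names five areas.

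**The concern.** Half of the planned sample exists only to fill the age-by-treatment cells, yet the allocation as described does nothing to fill them evenly. Two things have to go right: the age mix must be close to 50-50, and treatment must divide close to 1:1 within each age group. The first is an assumption. The second could be secured by design, because age is known before randomisation.

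What is at stake is the precision of the subgroup comparison that doubled the trial. Allocation is carried out at enrolment, so an uneven split cannot be undone at analysis. The allocation method belongs in the protocol, which has a section for it, so this is not a detail that can wait for a statistical analysis plan.

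**Working it through.** **Inputs (Sample size section):** margin 6.8, SD 10, significance level 0.05, power 80%, 27 per group before dropout, 30 per cell, 120 in total. **Assumptions added here:** one-sided 5%, because it reproduces the stated 27, and a true difference of zero. The protocol states neither.

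**1. Reproduce the plan's figure.** n = 2 × SD² × (z₀.₉₅ + z₀.₈₀)² / margin² = 2 × 100 × (1.645 + 0.842)² / 46.24 = 26.7, so 27 per group. One-sided 2.5% would give 34. Four cells of 30 make 120, as stated.

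**2. How far a cell can stray from 30.** Take exactly 60 children in an age group.
- Simple 1:1 randomisation: the cell is Binomial(60, 0.5), SD 3.9, 95% range 22 to 38. The chance of 35:25 or worse is 2 × P(X ≤ 25) = 0.245. The chance that the smaller cell is below 27 is 2 × P(X ≤ 26) = 0.366.
- Arm totals held at 60:60, no age strata: the cell is Hypergeometric(120, 60, 60), SD 2.75, 95% range 25 to 35. The same two chances are 0.100 and 0.201.

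**3. Let the age mix vary as well.** Each child is under 12 with probability 0.5. The event is that at least one of the four cells falls below 27.
- Simple randomisation (multinomial simulation): 0.77.
- Arm totals at 60:60: each arm's under-12 count is Binomial(60, 0.5), independently, so 1 − (1 − 0.366)² = 0.60.
- Allocation balanced within age group: this happens only if fewer than 54 or more than 66 of the 120 children are under 12, so 0.24.

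**4. What an uneven split costs.** Power within one age group = Φ(6.8 / (10 × √(1/n₁ + 1/n₂)) − 1.645).

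| Split between arms | Standard error | Power |
|---|---|---|
| 30:30 | 2.582 | 0.839 |
| 35:25 | 2.619 | 0.829 |
| 38:22 | 2.679 | 0.814 |

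Averaged over the binomial distribution, power is 0.833, a loss of 0.6 of a percentage point from 0.839.

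**5. What stratification does not repair.** If the age mix is 60:40, the smaller age group has 0.40 × 120 / 2 = 24 per arm and power 0.761. At 70:30 it has 0.30 × 120 / 2 = 18 per arm and power 0.654. These are before dropout. When the mix varies around 60:40, average power in the smaller age group is 0.750 with simple randomisation and 0.758 with age strata, which is almost no difference.

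**The case against.** The strongest reply is that the protocol is silent on stratification and does not exclude it. A computer-generated list may be blocked or stratified, so no statement in the protocol is broken. This stands in part. A reader might infer that simple randomisation was used, but the text does not say so. That is why the chances above are ranges, and the 25% is only the upper end. If the list is already stratified by age, one sentence settles the matter.

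A second reply is that the power cost is about one percentage point at 35:25 and that power stays above 80% even at 38:22. This is correct, and it limits the weight of the point.

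Two stronger readings are tempting and should be resisted.
- A reader might infer that imbalance confounds the subgroup comparison by age. Within an age group the age category is constant and treatment is randomised, so unequal arm sizes cost precision only. The age contrast in the Statistical analysis section, younger against older children within one treatment, is not a randomised contrast, and stratifying treatment by age would not change that.
- A reader might attribute the fall to 76% or 65% power to the missing stratification. It comes from an uneven age mix, which no allocation method can alter.

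The overall comparison at 60 per arm is not threatened either: on the same formula its power is about 98% before dropout.

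**Conclusion.** The point holds as a mismatch between two sections. The Sample size section depends on four cells of 30, and the Randomization section names nothing that keeps treatment balanced within age group. Without age strata, at least one cell would fall below 27 in about 60% of trials (arm totals fixed) to 77% (simple randomisation). With age strata this falls to about 24%, at the same total of 120. The loss in power is small, from 0.839 to between 0.83 and 0.81 for plausible splits. This is therefore a cheap improvement in design, not a threat to the trial's main conclusion.

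The chances assume a 50-50 age mix. The powers rest on one-sided 5%, a true difference of zero, an SD of 10 and a normal approximation, all before dropout. The dependence on the 50-50 age split is a separate weakness, larger in power terms, and stratification does not address it.

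**What to change.** - **Randomization:** state that the list is generated in concealed permuted blocks of varying size, stratified by age group (under 12; 12 and over). Hospital area can be an optional second factor. Five areas by two age groups make ten strata, about 120 / 10 = 12 children each on average, some of them sparse. Age alone needs two strata. If the existing list is already stratified, say so.
- **Statistical analysis:** account for age group in the primary comparison, for example by an age-stratified rank-sum test (van Elteren), or by a model with age group as a factor. Either replaces the unstratified rank-sum test now named, and the change of method should be acknowledged.
- **Sample size:** beside the 50-50 assumption, state that at 60:40 and 70:30 the smaller age group has about 24 and 18 per arm before dropout, with about 76% and 65% power. If 30 per cell is essential, an age quota or recruitment by age group would also be needed.

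The cost is regenerating the list for the remaining enrolment and adding a few sentences. The total stays at 120, and no new data are needed because age is already recorded at baseline. If enrolment has closed, only the analysis and power statements can still be changed.

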### **Blinding**

This trial tests a clinical intervention that is not suitable for protection against treatment bias. Recruiter will be blinded. Consultant on duty at will perform randomization and allocation. Non-operative treatment will be started immediately after recruitment. ORIF will be performed by surgeon on duty. Surgeon is not blinded. Trial data is collected at each appointment at the outpatient clinic by a physicians not related to the trial. Statistician analyzing trial data is blinded to treatment group.

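### The protocol contradicts itself on who randomises and whether the recruiter is blinded, and leaves concealment of upcoming allocations unsecured

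*Protocol*

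**What the plan says.** Three sections of the protocol describe who handles the allocation and who knows it.

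- **Study design:** "Trial data analysts and person performing the recruitment will be unaware of the assigned treatment".
- **Randomization:** "After agreeing to participation in the trial patients are randomized according to a computer-generated randomization list". The section then gives the ratio ("Randomization ratio is 1:1") and names the person: "Randomization is performed by the recruiting physician who is blinded to the intervention".
- **Blinding:** "Recruiter will be blinded. Consultant on duty at will perform randomization and allocation".

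The Patient's choice arm section lets eligible families who decline randomisation pick either treatment and stay in the same follow-up. The Statistical analysis section allows that arm to be merged with the corresponding randomised group, depending on group size.

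**The concern.** Two different roles are given one task, and a property is claimed for one of them that the task rules out. Whoever draws an allocation from a list learns it. If the recruiter draws it, the recruiter is not blinded, whatever the Study design and Blinding sections say.

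The wording also confuses two protections. Blinding concerns who knows the allocation after it has been made. Concealment concerns whether anyone can know the next allocation before a patient is irrevocably enrolled. Concealment is what prevents selection at entry. The Randomization section puts the enroller in charge of the list-based step and offers blinding as the protection.

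Selection at entry would matter in this trial for four reasons:

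- The surgeon is not blinded, and the Blinding section concedes that the intervention cannot be protected against treatment bias.
- The primary outcome, QuickDASH at 12 months, is reported by patients and guardians.
- Screening is done by surgical specialists, and the Ethics and dissemination section says that treatment varies with the clinic and the treating surgeon. Some of those who enrol may therefore hold a preference.
- A family steered away from randomisation is not lost to the study. It can enter the choice arm, and its data may return to the comparison through the merger.

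**Working it through.** The point rests on no figure in the protocol, so the check sets the sections side by side.

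**Step 1: who does what**

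| Section | Who randomises | What the recruiter knows |
|---|---|---|
| Study design | not stated | not the allocation |
| Randomization | the recruiting physician | said to be blinded |
| Blinding | the consultant on duty | said to be blinded |

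**Step 2: can all three be true?** The protocol does not say whether the recruiter and the consultant on duty are the same person, so both cases are needed.

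- *Same person.* The Randomization and Blinding sections then agree on who randomises. That person draws the allocation and so knows it. The blinding statements in all three sections fail.
- *Different people.* If the consultant randomises, the recruiter can remain unaware, and the Study design and Blinding sections can both hold. The Randomization section is then wrong about who randomises. If instead the recruiter randomises, the Blinding section is wrong about who does it, and the recruiter-blinding statements in all three sections fail.

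No case makes every statement true. A site that follows the Randomization section and a site that follows the Blinding section would run different procedures.

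**Step 3: is concealment secured?** The relevant statements are these:

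1. Randomisation comes after agreement to take part (Randomization section).
2. It uses a computer-generated list (same section).
3. The person operating that step is the one who recruits (same section).
4. The only protection named for that person is blinding (same section).
5. No section says who holds the list or whether later entries are hidden from the enroller.

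Statement 1 fixes the order of consent and draw for a given patient. It does not establish that the recruiter was ignorant of the next entry before approaching the family. If the recruiter works from a visible list, the next entry can be read in advance. If the recruiter requests one allocation at a time from a closed source, it cannot. The text fits both arrangements. Statement 4 does not decide between them, because Step 2 shows that it is untrue for a recruiter who randomises.

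**Step 4: size.** A bias in QuickDASH points would need two inputs: how often allocations were foreseen, and how far diverted patients differ in prognosis. The protocol gives neither, so no figure is computed.

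**The case against.** The strongest reply has five parts.

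1. *The Blinding section can stand on its own.* If the consultant on duty is not the recruiter, recruiter blinding holds. This is correct, and it limits the failure to the Randomization section's procedure or to the case where the two roles coincide. It does not remove the contradiction, because the Randomization section then names the wrong person.

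2. *Concealment may be intact.* A reader might infer that concealment cannot hold under this protocol. The document does not support that. Randomisation follows agreement, no section says that upcoming allocations are visible, and a recruiter can trigger a concealed allocation. The word blinded in the Randomization section may even be a clumsy way of saying that the recruiter does not know what comes next. What stands is narrower: the text does not secure concealment, and the safeguard it offers is the wrong one.

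3. *Silence on method is not an error, and the list carries a citation that has not been seen.* Silence alone would deserve only a remark. Here the protocol makes a positive statement about who operates the list and with what protection, and that statement is faulty.

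4. *The choice arm is closed to allocated patients.* A reader might infer that a patient could be moved there after an unwelcome draw. As written, the arm is offered only to families who refuse randomisation, so the protocol provides no such route. The remaining exposure lies before consent and depends on the next allocation being foreseeable.

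5. *Baseline data would reveal imbalance.* Displacement, age, and main sport or instrument with its level are recorded at baseline, and an analysis plan that is not shown might adjust for them. That would help with measured factors. It cannot repair selection on unmeasured ones, and the Wilcoxon rank-sum test named in the protocol makes no adjustment.

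**Conclusion.** The contradiction is established from the text alone: the Study design, Randomization and Blinding sections cannot all be right about who randomises and whether the recruiter knows the result. That conclusion needs only the premise that a person who draws an allocation learns it.

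The second conclusion is weaker and should be stated as such. Concealment of upcoming allocations is unsecured, not shown to be broken. It becomes a bias only if enrollers could in fact foresee allocations and acted on them, and the document is evidence for neither.

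The size is unknown. A reader might want to turn the risk into an inflated rate of false non-inferiority, but any such number would rest entirely on an assumed bias for which the protocol gives no basis.

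The procedure should still be changed, because it is wrong as written, the correction is cheap, and selection at entry would be hard to detect or undo in an open trial with a patient-reported outcome.

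**What to change.** Rewrite the Study design, Randomization and Blinding sections so that they describe one procedure:

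- The recruiter screens, takes consent and irrevocably registers the patient as randomised.
- Only after registration is the allocation released, by one named source independent of recruitment. This can be a central web or telephone service or, at minimum, sequentially numbered sealed opaque envelopes held by someone outside recruitment.
- The protocol states who holds the list and that recruiters have no access to it.
- The statement that the person who randomises is blinded is deleted. Recruiter blinding is claimed only if the recruiter has no part in the draw and is not told its result.

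The cost is a wording amendment to three sections and a standard randomisation tool or a set of envelopes. It needs no extra patients, visits or assessors.

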### **Patient's choice arm:**

Patients who meet inclusion criteria, but refuse participation in the randomized trial are offered to choose treatment method (operative or non-operative) and continue in a prospective parallel patient preference arm that otherwise follow the same treatment and FU protocol as the RCT.

## **Baseline**

Standard anterior-posterior and lateral radiographs of the elbow will be obtained after closed reduction of the possible elbow dislocation. All participants in either the RCT or patient's choice arm undergo cone-beam or normal computer tomography (CT) before treatment initiation. Initial fracture dislocation will be calculated from the CT scans in three planes (anterior-posterior, cranial-caudal and medial-lateral) and both radiographs (anterior-posterior and lateral) using the method described by Edmonds et al (2010). Date of injury, method of injury, patient's age at time of injury, sex, injured side, dominant hand and main sport or musical instrument as well as level will be documented. Motor and sensory function as well as range of motion of both upper limbs will be assessed. Carrying angle (degrees) and valgus stress test will be assessed if possible for both limbs.

## **Intervention**

Non-operative treatment means upper limb immobilization with forearm in neutral pro-supination with a long arm cast for 4 weeks. Treatment is started after baseline examination.

Operative treatment is scheduled after baseline examination and is to be done within 7 days from injury. During sedation both elbows are stress tested using the valgus stress test, any instability is documented, carrying angle of both elbows are measured. Procedure of preference is open reduction and internal fixation (ORIF) with cannulated non-resolvable 4.0 mm screw with or without washer. If the fracture fragment is too small or fragmented for screw fixation 1.6 mm – 1.8 mm Kirshner-wires and/or bone anchor are used. After fracture fixation the injured side is again stress tested. Radiographs (anterior-posterior and lateral) documenting the fixation are taken. Long arm cast with forearm in neutral pronation is applied for 4 weeks. Time from injury to surgery, fixation method, length of surgery (min) and surgeon's level of training (consultant, registrar) will be documented. Hardware is not routinely removed.

All patients will receive a written exercise plan explaining the active and passive ROM exercises that are to be performed at a minimum three times per day from cast removal. Physiotherapy will be offered if guardians and/or patients feel that no progress in ROM after 2 weeks of home exercises.

### **Blinding**

This trial tests a clinical intervention that is not suitable for protection against treatment bias. Recruiter will be blinded. Consultant on duty at will perform randomization and allocation. Non-operative treatment will be started immediately after recruitment. ORIF will be performed by surgeon on duty. Surgeon is not blinded. Trial data is collected at each appointment at the outpatient clinic by a physicians not related to the trial. Statistician analyzing trial data is blinded to treatment group.

### **Outcome measure**

Follow-up is set at 1, 3, 6, 12 and 24 months from initiation of treatment with the option of ending the FU at 12 months if patients is pain free with full ROM in relation to uninjured side. Elbow standard radiograph (anterior-posterior and lateral) are taken at each appointment from 3 months on until bone union is achieved or trial ends (Table 1).

Patients will be examined at the pediatric orthopedic outpatient clinic. Upon each appointment active and passive ROM of both upper limbs (elbow extension-flexion, pro-supination, wrist extension-flexion) as well as carrying angle are measured using a goniometer. Stability of both elbows are assessed using the moving valgus test and the valgus stress test. Distal sensation is examined by Semmes-Weinstein monofilaments. Signs of cold intolerance will be assessed. Grip strength is measured with a dynamometer.

Patients and guardians are requested to answer the following patient reported outcome measures at each appointment; QuickDASH, Pediatric Quality of Life InventoryTM (PedsQL), PedsQL Pediatric Pain Questionnaire, cosmetic visual analogue scale (VAS 0-100) and Mayo elbow performance score (MEPS).

Time of returning to main sport or music and its level will be documented (weeks). Any adverse effects (wound infection, nerve damage) are documented as well as hardware problems and possible hardware removal as well as conversion of treatment during FU (cast to ORIF or ligament reconstruction).

